### Primary endpoint

#### Non-inferiority

Cumulative 24 h opioid consumption and average pain NRS score at 24 h after surgery is the primary joint endpoint, which will be analyzed by “joint hypothesis test.” In this analysis, the intervention group could be considered effective as long as either of the two endpoints is non-inferior. The confidence interval method will be used to perform the non-inferiority test, and the result will be expressed as effect size (difference) (95% CI). If the effect size upper limit of the one-side 95% CI is smaller than 5 in cumulative 24 h opioid consumption, we will conclude that ESPB is non-inferiority to TPVB; in addition, when average pain NRS scores at 24 h after surgery is smaller than 1, ESPB group will be also considered non-inferiority.

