## Strengths and limitations of this study

Our study is the first trial in non-inferiority, double-blinded design of comparing ESPB with TPVB for analgesia in laparoscopic nephroureterectomy.The primary outcome in our study is set as a joint endpoint of opioid consumption and pain NRS scores, both of which are deemed equal important in evaluating pain control.This study will investigate not only erector spinae plane block efficacy of analgesia, quality of postoperative recovery as usual, but also its clinical features of blockage.The relatively small sample size may limit to discriminate the safety consideration between the two blocks technique.A single-center trial design may limit its universality.

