### Endpoints

#### Primary endpoint

The primary outcome in this trial is a joint endpoint of cumulative 24 h opioid consumption after surgery and average pain NRS score at 24 h (valued the average from NRS score at rest and with movement at 24 h) postoperatively.

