#### Superiority

If non-inferiority is conducted for the primary outcome, the superiority of the corresponding comparison will be evaluated for each outcome using an overall *α* of 0.025 with Holm-Bonferroni correction for testing both outcomes (upper limit of 97.5%CI smaller than predefined margin for most significant outcome and upper limit of 95% CI for the other). If superiority is detected on at least either cumulative 24 h opioid consumption or pain NRS scores, the ESPB group will be claimed to be better than TPVB group.

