## Discussion

Clinical anesthesiologists are always looking for a more convenient, effective, and safer analgesic method to control acute pain after surgery. Regional block has become an important role of perioperative multimodal analgesia nowadays. ESPB is thought to be a promising inter-fascial block due to its reliable opiate-sparing effect and easy performing characteristic [30]. Although evidence is increasingly that ESPB is an effective analgesic measure in thoracic surgery, there is still lack of proofs in urological surgery.

Epidural block was recognized as the golden standard analgesia in abdominal surgery in the past decades; however, regional block is mounting to an important position in the area of acute pain management for its convenience and safety. Paravertebral block is deemed as a premium alternative to epidural block and has been used for many years in various kinds of surgery due to its definite analgesia [31]. Most of the recent studies have compared ESPB with intravenous analgesia; however, there is still lack of study comparing ESPB with TPVB except Taketa and colleagues’ work [9]. What is more, the mechanism by which ESPB works through paravertebral space remains conflicting [15]. Therefore, the distribution of sensory loss as well as its analgesic duration also becomes our research interests. Our results will provide new evidence of ESPB into these aspects.

As for pain evaluation, most studies have concentrated on the opioid consumption or pain severity separately, but in fact, these two components contribute equal importance to pain evaluation [32]. Therefore, our research set two endpoints as a joint endpoint to resolve this dilemma. We expect that ESPB with its own merits will be non-inferior to TPVB.

UTUC patients undergoing laparoscopic nephroureterectomy are deemed as a good observation population, due to the incisions of this surgery located both in the lateral and lower abdomen wall and the high incidence of moderate-severe pain after surgery. To our knowledge, this study is the first one to compare ESPB with TPVB in regard to the efficacy and safety in patients undergoing laparoscopic nephroureterectomy. The result might have an influence on enhanced recovery (ERAS) management in urological surgery.

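### ESPB is declared non-inferior if either opioid use or pain score passes, so it can succeed while clearly worse on the other half of the joint endpoint

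*Protocol article*

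**What the plan says.** The Primary endpoint section under Endpoints defines one outcome with two components: "The primary outcome in this trial is a joint endpoint of cumulative 24 h opioid consumption after surgery and average pain NRS score at 24" hours. Two sections give the reason. Strengths and limitations describes the components as "both of which are deemed equal important in evaluating pain control". The Discussion says that "these two components contribute equal importance to pain evaluation", notes that most studies look at the two separately, and continues: "Therefore, our research set two endpoints as a joint endpoint to resolve this dilemma".

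The Non-inferiority section of the Statistical analysis then sets the rule: "In this analysis, the intervention group could be considered effective as long as either of the two endpoints is non-inferior". It gives two routes, each ending in a non-inferiority conclusion. The opioid route is "If the effect size upper limit of the one-side 95% CI is smaller than 5 in cumulative 24 h opioid consumption". The pain route is "when average pain NRS scores at 24 h after surgery is smaller than 1, ESPB group will be also considered non-inferiority". I read the pain route as also referring to the upper confidence limit of the difference, since the sentence runs parallel to the opioid one. Nothing in the article requires the component that did not pass to be no worse.

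The Superiority section, entered once non-inferiority is met, also allows a claim on either component, but there "with Holm-Bonferroni correction for testing both outcomes" is specified. No such correction appears at the non-inferiority step.

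**The concern.** The rule does not match the claim. Study objectives states a single hypothesis, that the analgesic efficacy of ESPB is non-inferior. If opioid use and pain matter equally, being no worse on one and clearly worse on the other does not establish that. An either-or rule returns to judging one component at a time, which the Discussion says the joint endpoint is meant to end.

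The design makes this a practical risk. Under Anesthesia management and postoperative analgesia, sufentanil is delivered as patient-controlled boluses with no background infusion. Patients with a weaker block can bring their pain down by pressing the button more often, so the deficit appears in opioid use while NRS looks similar. The reverse, similar opioid use with more pain, is also possible, though that is inference. Either way the rule lets ESPB pass on the component that does not show the deficit.

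A second problem follows. Two chances to succeed, each at one-sided 5% and uncorrected, raise the error rate above 5%, although the plan recognises this for its either-or superiority step.

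At stake is the trial's headline conclusion, and also the gate to superiority testing, where a win on one component would let ESPB be called better.

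**Working it through.** **Inputs from the protocol.** Margins: 5 μg and 1 NRS point. NRS SD: 2.5. Size before attrition: 77 per arm, 1:1. Limits: one-sided 95%. Pilot means: 25.7 μg (SD 2.0) with TPVB and 35 μg (SD 14.0) without block, a gap of 35 − 25.7 = 9.3 μg.

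**Assumptions.** The article names neither the opioid SD used for planning nor a correlation between components. I take the SD that 77 per arm implies and vary the correlation.

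**The plan's own sample sizes** (one-sided 5%, 90% power, true difference 0; (1.645 + 1.282)² = 8.564):
- Opioid with the pilot SDs: 8.564 × (2.0² + 14.0²) / 5² = 68.5, so 69 per arm, not 77. Solving 77 for a common SD gives √(77 × 25 / (2 × 8.564)) = 10.6 (about 10.5 with t limits).
- NRS: 2 × 8.564 × 2.5² / 1² = 107.05, so 108 per arm, not 70. Seventy would need an SD of about 2.0.

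Neither figure reproduces, so SDs are varied below. The finding itself does not depend on them.

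**Chance that one component passes.** With SE = SD × √(2/77) = SD × 0.1612 and a t critical value of 1.655 (152 df):

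pass probability ≈ Φ((margin − true difference) / SE − 1.655)

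The SEs are 10.5 × 0.1612 = 1.692 μg and 2.5 × 0.1612 = 0.403 points.

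**Both true differences at their margins.** Each passes with probability 5%. At independence the either-or rule errs 1 − 0.95² = 9.75% of the time. Simulation gives about 9.2% at correlation 0.3, 8.8% at 0.5 and 7.5% at 0.8. The ceiling is 10%.

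**Opioid worse by 9.3 μg.** The opioid component almost never passes: (5 − 9.3)/1.692 − 1.655 = −4.20, probability about 0.00001. The either-or result is therefore the NRS result:

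| True NRS difference | Calculation | Declared non-inferior, either-or | Both required |
|---|---|---|---|
| 0 | 1/0.403 − 1.655 = 0.83 | 80% | about 0% |
| 0.3 | 0.7/0.403 − 1.655 = 0.08 | 53% | about 0% |
| 0.5 | 0.5/0.403 − 1.655 = −0.41 | 34% | about 0% |

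With NRS SD 2.0 the either-or column becomes 93%, 70% and 46%.

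**Pain worse by 2 points (twice the margin), opioid equal.** 5/1.692 − 1.655 = 1.30, so either-or declares non-inferiority 90% of the time (93% with opioid SD 10). With both required it is about 0%.

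**Power if both are required and the techniques are truly equal.** At independence 0.903 × 0.796 = 72%, rising to 73.5% at correlation 0.3 and 75% at 0.5. With NRS SD 2.0 it is 83–85%. With opioid SD 10 and NRS SD 2.5 it is about 74% at correlation 0 and 78–79% at 0.8.

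**The case against.** An at-least-one rule is a recognised design, and calling two components equally important does not by itself mean that both must pass. Both estimates with confidence intervals would presumably be published, so a reader could see a failed component. The 9.3 μg case is extreme, since ESPB would then spare no opioid relative to no block. The correlations and the opioid SD are assumptions. Multiplicity detail might sit in an analysis plan that is not shown.

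Some of this stands. The 9.3 μg scenario illustrates the rule and is not a forecast, and the percentages move with the SDs. The defect lies in the formal conclusion; no data are concealed.

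The rest does not rescue the rule. An at-least-one design needs alpha control and a claim confined to the component that passed; the Non-inferiority section states unadjusted limits and a general conclusion. Splitting alpha would repair only the error rate: at one-sided 2.5% each it is 1 − 0.975² = 4.9% at independence, yet with opioid 9.3 μg worse and pain equal, ESPB would still pass about 70% of the time. The sample size section also carries forward the larger of the two component sizes, which suits a rule requiring both. The either-or sentence may therefore be a slip, but it is explicit and governs the analysis.

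The most substantial objection is cost: requiring both leaves roughly a one-in-four chance of failure when the techniques are truly equal. That must be disclosed, but it is no reason to keep a rule that does not test the hypothesis.

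**Conclusion.** The concern holds and must be fixed. As written, one component alone can establish non-inferiority however poor the other is. With 77 per arm, opioid SD 10.5 and NRS SD 2.5, ESPB would be declared non-inferior about 80%, 53% or 34% of the time while costing 9.3 μg more sufentanil, at true NRS differences of 0, 0.3 and 0.5. It would be declared so about 90% of the time while 2 NRS points worse. False non-inferiority with both differences at their margins is 8.8–9.75% for correlations of 0.5 to 0, against a nominal 5%. The calculations assume approximately normal mean differences. The sizes shift with the SDs and correlation, but the flaw follows from the wording and appeared at every value tried.

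**What to change.** Replace the either-or sentence and the two separate routes with one rule: ESPB is non-inferior to TPVB only if the upper confidence limit for the difference (ESPB minus TPVB) in 24 h sufentanil consumption is below 5 μg **and** the upper limit for the difference in 24 h average NRS is below 1. State explicitly that the NRS criterion applies to the confidence limit. This is an intersection-union test, so each component keeps the full one-sided alpha. Open superiority testing only after both criteria are met.

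Restate power for the joint conclusion: about 72–75% at 77 per arm with SDs of 10.5 μg and 2.5 points, or 83–85% if an NRS SD of 2.0 can be justified.

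The rule itself costs a protocol and analysis-plan amendment before database lock and a less favourable stated power, with no new data or patients. Whether to accept that power is a separate sample-size decision for the sponsor. If 90% joint power is wanted with NRS SD 2.5, NRS alone sets a floor of 108 evaluable per arm. At independence about 118 are needed: the SEs become 1.367 and 0.325, the component powers about 0.978 and 0.922, and their product 0.90.

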### Randomization, allocation concealment, and blinding

#### Randomization

The SAS 9.3 software package (SAS Institute, Cary, NC, USA) is used to generate random numbers with a block size of 4 by biostatisticians who will not participant in the statistical analysis of the data. The random sequence will be sealed in consecutively numbered opaque envelopes and kept by the study coordinator. Participants will be randomly divided into two groups according to the 1:1 ratio of ESPB group and TPVB group. A research coordinator is designated to distribute and preserve randomization result. The coordinator will open the envelopes for allocation according to the order of enrolment and prepare the study drug.

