### Anesthesia management and postoperative analgesia

Intraoperative anesthesia management is performed by an attending anesthesiologist and an assistant; none of whom has knowledge of the allocation. Prednisone methylprednisolone (40 mg) is administered before anesthesia induction, followed by intravenous anesthesia induction with sufentanil (0.1–0.3 μg/kg), propofol (1–2 mg/kg), and rocuronium (0.6 mg/kg). Anesthesia is maintained by intravenous anesthesia combined with or without N_2_O/sevoflurane inhalation to maintain sedation level within the range of 40–60 under bispectral index (BIS) monitor. Opioid analgesics (remifentanil TCI together with sufentanil intermittent administration on demand) are used to maintain analgesia. During the surgery, the fluid volume and infusion speed are adjusted according to hemodynamic monitoring conditions to maintain the blood pressure within 20% of the baseline values. All surgical procedures are performed by fixed surgical team members, and the pneumoperitoneum pressure is often maintained at 12–16 mmHg as usual. After the surgery, standardized patient controlled intravenous analgesia pump is applied for each patient, which was established with 1.25 μg/ml sufentanil and programmed to deliver 4-ml boluses with a lock-out interval of 10 min and no background infusion rate. Patients who are enrolled for this trial will be trained to use a patient controlled intravenous analgesia pump before surgery.

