### Data collection and management

Baseline data will be collected, including age, gender, birth date, education years, weight, and height. Co-morbidities as well as important laboratory tests and instrumental examination will be documented. Preoperative recent sleep quality will be assessed with Pittsburgh Sleep Quality Index (PSQI) [26]. Intraoperative data, including duration of anesthesia and surgery, surgical information, and anesthesia medication including opioid consumption and fluid balance will be documented. Pneumoperitoneum pressure will be documented as an average throughout the operation. Outcome data will be evaluated and recorded according to the follow-up plan to ensure all timepoints data are noted.

Based on the original observation records of the participants, the data are collected into the case report forms timely, completely, and correctly. All data will be kept confidentially. Data entry will be performed in a double-input and double-check way with the REDCap (Research Electronic Data Capture) database system developed by the Vanderbilt University. The data will be monitored and sampled regularly in the trial by the Clinical Research Ethics Committee, and the database will be locked after the electronic data is checked. After data entry and verification as required are completed, the case report forms will be filed in numbered order and kept in a specific filing cabinet. We have no plan in interim analysis until the target sample size is achieved.

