## Statistical analysis

### Sample size calculation

The primary endpoint of this non-inferiority trial is the joint of cumulative 24 h opioid consumption after surgery and average pain NRS score at 24 h postoperatively.

In a pilot investigation of our patients, the mean (± standard deviation) of the cumulative 24 h opioid (sufentanil) consumption after laparoscopic nephroureterectomy was about 25.7 (± 2.0) μg with TPVB and 35 (± 14.0) μg with non-block respectively (data were unpublished yet). The non-inferiority margin was set as 5 (unit: μg; clinical practice treated it as an acceptable difference) [27]. With a significance level of *α* = 0.05 and a power of 1-β = 90%, the sample size required to detect difference was 77 patients in each group.

A 1–1.3 point difference in pain NRS scores is usually considered as acceptable subjective pain discrimination [28]. When the standard deviation of the pain NRS score was assumed as 2.5 and the non-inferiority margin of NRS was 1 score [29], 70 samples were estimated per group.

Hence, the greater sample calculated above was 77 participants per group. Considering a dropout rate of 5% and technique failure rate of 3%, we finally planned to enroll 83 participants per group (a total of 166 participants). The sample size was estimated by the PASS software (version 11.0; NCSS PASS, UT, USA).

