### Endpoints analysis

Baseline characteristic will be compared according the data distribution and type. In addition to graph method for qualitative analysis, Shapiro-Wilk test will be also used for quantitative analysis in review of data distribution. Continuous data with normal or approximate normal distribution will be expressed as mean ± standard deviation, while continuous data with non-normal distribution is expressed as median (interquartile, IQR). Continuous data will be tested by independent sample *t* test or Mann-Whitney *U* test according to data distribution. Categorical data will be expressed as numbers (percentages) and tested by chi-square test/Fisher’s exact test. Time-to-event data will be analyzed by the Kaplan-Meier estimator, with the difference between groups tested by the log-rank method. Two-tailed *p* values of less than 0.05 are regarded as statistically significant. All statistical analyses are performed with the SPSS 25.0 statistical package (IBM SPSS Inc., Chicago, IL, USA).

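### Optional gain in precision: the article names only unadjusted comparisons for the primary endpoint although age, gender, weight and PSQI are collected at baseline

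*Protocol article*

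**What the plan says.** The Non-inferiority section of the protocol article decides each primary component by a confidence limit against a margin: 5 μg for cumulative 24 h sufentanil and 1 point for the average NRS score. On the estimate it says only that "the result will be expressed as effect size (difference) (95% CI". It names no model and no covariate.

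For between-group comparison in general, the Endpoints analysis section says: "Continuous data will be tested by independent sample *t* test or Mann-Whitney *U* test according to data distribution". Neither test adjusts for anything.

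The Data collection and management section lists what is known before treatment: "Baseline data will be collected, including age, gender, birth date, education years, weight, and height". It adds: "Preoperative recent sleep quality will be assessed with Pittsburgh Sleep Quality Index (PSQI". Endpoints analysis compares baseline characteristics between groups but gives them no role in the primary estimate.

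The Randomization section says that the software is used to "generate random numbers with a block size of 4" and states no stratification factor.

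**The concern.** An unadjusted comparison of each primary component is the natural reading of the methods named, although the article never uses the word. It leaves in the error term any outcome variation that age, gender, weight or PSQI could explain. Non-inferiority is judged by an upper confidence limit, so the width of the interval bears on the conclusion for each component.

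A linear model with prespecified baseline covariates estimates the same mean difference. It can be held against the same margins and needs no new data. At stake is a modest amount of precision, not the validity of the result.

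**Working it through.** **Inputs from the article (Sample size calculation; Non-inferiority).** Opioid margin 5 μg; pilot SDs 2.0 μg (TPVB) and 14.0 μg (no block). NRS margin 1, SD 2.5. Stated sizes 77 per group (opioid) and 70 per group (NRS), with 77 used. The sample-size text reads "With a significance level of *α* = 0.05 and a power of 1-β = 90" per cent and does not say whether α is one- or two-sided. The decision rule uses a one-sided 95% limit, so one-sided 0.05 is the main case here.

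**Assumptions.** True difference 0, 1:1 allocation, and opioid SD 10, the root mean square of the two pilot SDs: √((2² + 14²)/2) = 10. R-squared, the share of outcome variance explained by the covariates, is not in the article and is varied.

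**Step 1: the plan's own figures.** n per group = 2 × SD² × (1.645 + 1.282)² / margin².
- Opioid: 2 × 100 × 8.564 / 25 = 68.5, so 69, against 77 stated.
- NRS: 2 × 6.25 × 8.564 / 1 = 107.05, so 108, against 70 stated.

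Neither figure is reproduced. That is a separate sample-size matter. It enters here only because it sets the starting power.

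**Step 2: power at 77 per group without adjustment.** Power = Φ(margin / (SD × √(2/77)) − 1.645), with √(2/77) = 0.1612.
- NRS: 1 / (2.5 × 0.1612) = 2.482; Φ(0.837) = 79.9%.
- Opioid: 5 / (10 × 0.1612) = 3.102; Φ(1.458) = 92.8%.

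**Step 3: power with adjustment.** Replace SD by SD × √(1 − R²). The interval half-width shrinks by the factor √(1 − R²).

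| Assumed R² | Half-width narrower by | NRS power | Opioid power |
|---|---|---|---|
| 0 | 0% | 79.9% | 92.8% |
| 0.05 | 2.5% | 81.6% | 93.8% |
| 0.10 | 5.1% | 83.4% | 94.8% |
| 0.20 | 10.6% | 87.1% | 96.6% |
| 0.30 | 16.3% | 90.7% | 98.0% |

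At one-sided 0.025 the pattern is the same. For R² of 0, 0.05 and 0.10, NRS power is 69.9, 72.1 and 74.4%, and opioid power is 87.3, 88.9 and 90.5%.

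**Step 4: the cost of four covariates.** Residual degrees of freedom fall from 154 − 2 = 152 to 148. Chance imbalance in four covariates multiplies the variance of the adjusted difference by about 1 + 4/(154 − 4 − 3) = 1.027, so the half-width by √1.027 = 1.0135. Net narrowing is then 1 − 0.975 × 1.0135 = about 1.2% at R² 0.05, and 1 − 0.949 × 1.0135 = about 3.8% at R² 0.10. At R² 0 the interval would be about 1.4% wider. The table is therefore slightly generous at its low end.

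**The case against.** The strongest objection is that nothing here is wrong. The Non-inferiority section does not fix an estimator, and covariates for the primary model are often left to the full protocol or SAP, which are not shown. This stands as far as it goes: the absence of a covariate list is not a defect. What remains is that the article does name its methods for continuous data, and they are unadjusted.

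A second objection also stands. With no stratification factor, a single centre and no listed baseline measurement of either endpoint, no design feature is being ignored.

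A reader might infer more than the article supports:

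- **That chance imbalance is left uncorrected.** The confidence interval of an unadjusted difference already allows for it.
- **That body weight must matter, because the pump is "programmed to deliver 4-ml boluses with a lock-out interval of 10 min and no background infusion rate" and use is counted in absolute μg.** The article gives no link between weight and use, and the block volume is itself scaled to weight (0.4 ml/kg). Suppose use were proportional to weight, with an assumed coefficient of variation of 15%. The spread from weight alone would be 25.7 × 0.15 = 3.9 μg, more than the whole pilot TPVB SD of 2.0 μg. No R-squared can be taken from this.
- **That the NRS component gains most.** Its power rises by more points in the table only because it starts lower. Nothing in the article suggests that the covariates predict pain scores better than opioid use.
- **That a wider interval leads directly to a failed trial.** The Non-inferiority section lets either component suffice. On the figures above, power for the overall claim is at least 92.8%, and about 98.5% if the components were independent (1 − 0.072 × 0.201).

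**Conclusion.** The point holds as a low-severity, optional efficiency improvement. The methods named are unadjusted, prognostic candidates are already collected, and adjustment keeps the estimand and both margins.

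At an assumed R-squared of 0.05 to 0.10, the interval narrows by about 2.5 to 5% (about 1 to 4% net of the four coefficients). By component, the gain is about 2 to 4 power points for NRS and 1 to 2 for opioid use, at 77 per group and one-sided 0.05. If the covariates explain almost nothing, there is no gain and a trivial loss. These sizes rest on the assumed R-squared, on SD 10 for opioid use and on a true difference of zero.

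Adjustment should not be read as a repair of the NRS sample size. Power of 90% at 77 per group would need an R-squared of about 0.3, which nothing in the article supports. That shortfall has to be dealt with separately.

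**What to change.** Before unblinding, add to the primary analysis a linear model for each component with treatment, age, gender, weight and PSQI as prespecified terms. Compare the upper confidence limit of the adjusted mean difference with the existing 5 μg and 1-point margins. Report the unadjusted difference as a sensitivity analysis. State that variables arising after randomisation, such as intraoperative drugs, will not be used for adjustment. If covariates are already fixed in the full protocol or SAP, a sentence saying so is enough.

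The cost is a few lines of text and four degrees of freedom, with no new data and no change to the sample size. There is time for it: the Trial status section describes recruitment as under way, and the Blinding section releases the allocation only after database lock.

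### The pain half of the primary non-inferiority rule names neither a between-group difference nor a confidence limit, and the sidedness of the reported 95% interval is left open

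*Protocol article*

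**What the plan says.** All of this stands in the Statistical analysis part of the protocol article.

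- **Method (Non-inferiority).** "The confidence interval method will be used to perform the non-inferiority test", and "the result will be expressed as effect size (difference) (95% CI"). The sidedness of that interval is not given.
- **Opioid criterion (Non-inferiority).** The condition is explicit: "If the effect size upper limit of the one-side 95% CI is smaller than 5 in cumulative 24 h opioid consumption".
- **Pain criterion (Non-inferiority).** The condition is that "when average pain NRS scores at 24 h after surgery is smaller than 1, ESPB group will be also considered non-inferiority".
- **Combination (Non-inferiority).** "the intervention group could be considered effective as long as either of the two endpoints is non-inferior".
- **Pain margin (Sample size calculation).** "the non-inferiority margin of NRS was 1 score". The assumed SD is 2.5. Alpha is given as 0.05 without sidedness.
- **Other levels.** Endpoints analysis sets a general rule that two-tailed p "values of less than 0.05 are regarded as statistically significant". Superiority uses an overall alpha "of 0.025 with Holm-Bonferroni correction for testing both outcomes".

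**The concern.** A non-inferiority criterion needs three elements: the contrast, the confidence limit with its level, and the margin. The opioid clause has all three. The pain clause has only the number 1. Its subject is a score, not a difference between groups, and it mentions no limit.

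This matters more than an ordinary slip of wording because either endpoint is enough. The incompletely stated half can carry the trial's main conclusion alone, and the choice between readings could be made after the results are known.

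A smaller matter sits beside it. The decision uses a one-sided 95% limit, which is the upper end of a two-sided 90% interval. The report is to show a 95% interval. If that is the usual two-sided interval, the paper could claim non-inferiority beside an interval that reaches past the margin.

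**Working it through.** **Inputs.** Pain: margin 1 point, SD 2.5. Opioid: margin 5 μg, pilot SDs 2.0 (TPVB) and 14.0 (no block). Planned size before allowance for losses: 77 per group. All are from Sample size calculation. The pilot gives no SD for ESPB, so using 14.0 for that arm is an assumption.

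**The plan's own figures.** With a true difference of 0, n per group = (s₁² + s₂²) × ((z for alpha + z for power) / margin)².
- Pain, one-sided 0.05, 90% power: 12.5 × (1.645 + 1.282)² gives 108, not the stated 70.
- Opioid, SDs 2 and 14, same alpha and power: 200 × (2.926 / 5)² = 68.5, so 69 to 70, not the stated 77.

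Neither figure is reproduced. That is a separate sample-size question. It matters here only because power for pain at 77 per group is below 90% before any change of alpha.

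**Readings of the pain clause at 77 per group.** SE of the difference = 2.5 × √(2/77) = 0.403.

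| Reading | Behaviour |
|---|---|
| (a) ESPB mean score below 1 | Not a comparison with TPVB. With an assumed true ESPB mean of 2, SE = 2.5/√77 = 0.285 and the chance of passing is Φ(−1/0.285) ≈ 0.0002, however TPVB performs |
| (b) Observed difference below 1 | At a true difference of 1: Φ(0) = 50%. At 1.3, the top of the discrimination range the article cites: Φ(−0.3/0.403) = 23% |
| (c) One-sided 95% upper limit of the difference below 1 | 5% at a true difference of 1 |
| (d) Upper limit of a two-sided 95% interval below 1 | 2.5% at a true difference of 1 |

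**Decision interval against reported interval, pain.** With 152 degrees of freedom:
- The one-sided 95% limit lies 0.667 above the estimate, so an observed difference up to 1 − 0.667 = 0.33 passes.
- The two-sided 95% limit lies 0.796 above it, so the interval stays below the margin only up to 1 − 0.796 = 0.20.
- The limits differ by 0.796 − 0.667 = 0.13 points. An observed difference between 0.20 and 0.33 passes on the first and crosses the margin on the second.

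**The same for opioid.** SE = √((2² + 14²)/77) = 1.61 μg. The limits lie 2.67 and 3.18 μg above the estimate, so they differ by about 0.5 μg. The window is 5 − 3.18 = 1.82 to 5 − 2.67 = 2.33 μg.

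**Power at 77 per group if the level moved to one-sided 0.025 (true difference 0).**
- Pain: 79.6% at one-sided 0.05, 69.4% at 0.025.
- Opioid, pilot SDs: 92.6% at one-sided 0.05, 86.9% at 0.025.
- Opioid, SD back-solved from 77: 5 × √(77/2) / 2.926 = 10.6. SE = 10.6 × √(2/77) = 1.708, so power at 0.025 is Φ(5/1.708 − 1.960) = Φ(0.967) ≈ 83%, against 90% by construction at 0.05.

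**The case against.** The best reply is that the pain clause is elliptical. The sentence before the two criteria commits the non-inferiority test to the confidence interval method and describes the result as a difference. The pain clause follows the opioid clause as a parallel condition. The sample-size section calls 1 point a non-inferiority margin, and a margin applies to a difference. The Superiority section also works with upper limits for both outcomes. On that reading, (c) is intended and the error rate for pain is 5%.

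Most of this stands. A reader might infer that the trial plans a point-estimate rule for pain, or that the false-positive rate of the pain component is uncontrolled. The documents do not support either inference: no point-estimate rule is stated, and the adjacent sentence points away from one. What remains is that the criterion has to be completed from neighbouring text, although the opioid criterion in the same sentence is written out in full.

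A reader might also infer that one-sided 5% is an error because two-tailed 0.05 and overall 0.025 appear elsewhere. That does not follow. One-sided 95% is stated explicitly for non-inferiority and is compatible with alpha 0.05 in the sample-size section. The other levels belong to general testing and to the later superiority step. The mismatch of intervals is likewise conditional, because the article does not say that the reported 95% interval is two-sided.

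**Conclusion.** The concern holds as a defect in how the primary decision rule is written. The pain half lacks the contrast and the confidence limit, and under the either-endpoint rule it can decide the trial. A bound on the difference is probably meant; the 50% pass rate at a true difference of 1 point is the cost of the worst-case reading only. Across the readings that test a difference, the error rate at the margin runs from 2.5% to 50%.

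The interval ambiguity is real but narrower. If the reported interval is two-sided, the claim and the published interval disagree for observed pain differences of about 0.20 to 0.33 points, or opioid differences of about 1.8 to 2.3 μg. These windows assume 77 analysed per group, an SD of 2.5 for pain, and SDs of 2.0 and 14.0 for opioid.

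The fall in power under one-sided 0.025 is no argument that the present level is wrong. Nor should the whole shortfall for pain be put down to such a change: about 10 points (79.6% to 69.4%) come from alpha, and the gap between 90% and 79.6% is already there.

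**What to change.** Replace the two criteria with one rule. For each endpoint, ESPB is non-inferior if the upper limit of the one-sided 95% confidence interval of the mean difference, ESPB minus TPVB, is below the margin: 5 μg for cumulative 24 h opioid consumption, 1 point for average NRS at 24 h. The plan's either-endpoint combination is left as it is here; its multiplicity is a separate question.

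State that the matching interval will be reported: the two-sided 90% interval or the one-sided 95% limit, beside any two-sided 95% interval. Say in the sample-size section that alpha 0.05 is one-sided.

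This is a sentence or two of text. It changes neither the stated level, the sample size nor the power. It should be fixed before the allocation is revealed for analysis; the article describes the trial as still enrolling.

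Moving to one-sided 0.025, so that decision and report both use the two-sided 95% interval, is an optional design change. At 77 per group it would lower pain power from about 80% to 69%, and opioid power to about 83% (back-solved SD) or 87% (pilot SDs).
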